### Randomization and blinding

Eligible subjects will be divided and stratified based on age (within 10-year intervals) randomly into two groups including control (standard weight-loss group + taking placebo, *n* = 25) and intervention (standard weight-loss group + Tau supplementation, *n* = 25). Randomization will be performed using the computer-generated random numbers by a third party to reduce the probable bias. The third party will generate a random block design in blocks of 10.The naming of Tau or placebo bottles will be done based on random numbers and odd or even numbers will be allocated randomly to groups A or B. To preserve the blindness in case of any side effects, the third party will use unique codes instead of A or B.To achieve blinding, the bottles will be sealed, and we will be assured from the similarity of appearance and their weight. The researcher and participants will be blinded to the treatment allocation. Randomization codes of the RCT will be unlocked only after all individuals complete the study protocol.

### Intervention

All subjects will follow a hypocaloric diet, whose energy needs will calculated by the Mifflin St. Jeor equation. Then, 30% of estimated energy requirements will deduct. The intervention group will receive 1-g Tau capsule three times a day after breakfast, lunch and dinner. The Tau supplementation dose will be determined according to the previous study [12].Tau supplement will be provided by Nutricost Company (Midvale, UT, USA). In addition, Placebo capsules will be provided by the Pharmacy Faculty of Ahvaz Jundishapur University of Medical Sciences in the same form and size as the Tau capsules. All capsules will be given to participants in the similar packing every 15 days. The macronutrients of a hypocaloric diet will be 50% carbohydrate, 30% fat and 20% protein. Considering the general principles of dieting, a trained dietitian will give a dietary exchange list and an individualized diet according to the subjects’ dietary habits. The same dietitian will follow the subjects to check compliance through phone calls or SMS every 3 days. Figure 2 shows the schedule for enrollment, intervention and assessment based on the Standard Protocol Items; Recommendations for Interventional Trials (SPIRIT) Figure.

**Fig. 2 Fig2:**
[figure not shown]
Schedule for enrollment, intervention and assessment based on Standard Protocol Items; Recommendations for Interventional Trials (SPIRIT) Figure

### Measurements

An individual information questionnaire including demographic situations, history of diseases, supplementations and medications will be filled at the baseline. Dietary intake will be evaluated by 3-day 24-h recall questionnaires (two weekdays and one weekend day) at the beginning, middle and the end of the study. Total calorie and macroniutrients intake will be calculated using Nut IV (the Hearst Corporation, San Bruno, CA, USA ). The participants will be asked not to change their physical activity level (PAL). Physical activity levels will be assessed by the International Physical Activity Questionnaire (IPAQ) at the beginning and end of the study. The physical and anthropometric measurements will be given with minimal clothing and without shoes. Body weight will be measured using a 100-g accuracy scale (Seca). Height will be measured using a 0.5-cm accuracy Seca stadiometer. BMI will be computed by dividing body weight (kg) to the square of height (m). Waist circumference will be measured using a tape meter at the midpoint between the lowest rib and iliac crest and at the end of a normal expiration to the nearest 0.5 cm. A TANITA BC-418 body analyzer will be applied to estimate total body fat, fat percent, fat-free mass and fat-free mass percent. Five milliliters of venous blood sample (in a regular tube) will be taken after a 10–12-h overnight fast at the baseline and end of the study. Blood samples will be centrifuged at 1500 g for 15–20 min to separate the serum. Serum will be stored at − 80 °C and will be used for biochemical analysis, such as FGF19 (μg/mL), FGF21 (μg/mL), β-klotho co-receptor (μg/mL), leptin (μg/mL), adiponectin (μg/mL), hs-CRP (μg/mL), insulin (μU/mL), fasting blood sugar (FBS) (mg/dL), total cholesterol (TC), high-density lipoprotein (HDL-C), triglyceride (TG), alanine transferase (ALT), aspartate transaminase (AST) and gamma-glutamyl transferase (GGT), in the serum. Enzyme-linked immunosorbent assay (ELISA) kits will be applied to measure serum FGFs, β-klotho co-receptor, leptin, adiponectin, hs-CRP and insulin, lipid profile and serum glucose concentration. Also, serum hepatic enzymes will be measured using the enzymatic method by Pars Azmoon kits (Tehran, Iran). Low-density lipoprotein (LDL-C) concentrations will be computed by the Friedewald equation. Homeostasis model assessment – insulin resistance (HOMA-IR) will be calculated as follows:$$ \mathrm{FBS}\ \left(\mathrm{mg}/\mathrm{dL}\right)\times \mathrm{fasting}\ \mathrm{serum}\ \mathrm{insulin}\ \left(\mu \mathrm{U}/\mathrm{mL}\right)/405, $$

where FBS is fasting blood sugar.

### Statistical analysis

We will use intention-to-treat (ITT) and per-protocol (PP) populations in the analysis. The ITT population consists of all individuals who will be randomized, whereas the PP population consists all participants who complete the 8-week intervention. The data will be revised randomly to check accuracy and completeness. All data will be reported as mean ± SD. The percentage changes for each variable will be computed by the following formula:$$ \left[\left(E-B\right)/\mathrm{B}\times 100\right], $$

where *E* and *B* are the end value and the baseline value of variable, respectively. The data normality will be analyzed using the Kolmogorov-Smirnov test. To compare parametric continuous data between and within the groups, the independent sample *t* test and the paired sample *t* test will be used, respectively. In addition, to compare the differences in asymmetric variables between and within the groups, the Mann-Whitney test and Wilcoxon test will be applied, respectively. The analysis of covariance (ANCOVA) test will be used to control confounding variables. To evaluate the association between changes in fibroblast growth factors (FGF19, FGF21), β-Klotho co-receptor concentrations and other variables, linear regression models will be used. SPSS version 21 (IBM, Armonk, NY, USA) will be used for data analysis. A *p* value < 0.05 will be considered statistically significant.

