### Sample size

The sample size was calculated based on the effect of Tau supplementation on changes in hs-CRP in obese people that was conducted by Rosa et al. [12]. It was computed by considering 95% confidence interval and 80% power (α = 0.05 and β = 0.2). In addition, the mean and standard deviation (SD) of hs-CRP levels in the mentioned study was as follows: μ_1_ = 14.30; μ_2_ = 10.50; SD_1_ = 2.90; SD_2_ = 2.40. We considered a 20% attrition rate. Finally, 25 subjects are considered for each group. All individuals will be included in the RCT if they meet the inclusion criteria and are willing to participate in the study to achieve the estimated sample size.

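### The PP set is defined by completion alone, and with serum drawn only at baseline and end, the ITT and PP serum analyses will largely coincide unless women who stop are still measured or have end values imputed

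*Protocol article*

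**What the plan says.** The Statistical analysis section announces two populations: "The ITT population consists of all individuals who will be randomized, whereas the PP population consists all participants who complete the 8-week intervention". It does not rank the two.

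The same section computes percentage change from E and B, which "are the end value and the baseline value of variable, respectively". For roughly normal variables, between and within groups, "the independent sample *t* test and the paired sample *t* test will be used, respectively". Mann-Whitney and Wilcoxon tests take their place for skewed variables, ANCOVA handles confounders, and linear regression relates changes to one another.

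Three other sections bear on this:

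- Measurements: venous blood is taken after an "overnight fast at the baseline and end of the study". The text gives no interim serum sample.
- Sample size: "We considered a 20% attrition rate", with 25 women per group.
- Intervention: a dietitian checks compliance by telephone or SMS every 3 days, and "All capsules will be given to participants in the similar packing every 15 days".

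**The concern.** An ITT and a PP analysis are normally reported side by side because they answer different questions. One compares the groups as randomised. The other asks what happens among women who followed the protocol. The comparison is informative only if the two sets differ, and differ by adherence.

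Here the PP set is separated from the ITT set by completion, not by how much of the supplement was taken or how closely the diet was followed. Completion is also what would ordinarily decide whether an end blood sample exists. A woman without an end sample drops out of each listed test, whichever population she nominally belongs to. The rule that defines PP and the mechanism that removes women from ITT could therefore pick out the same people.

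Two things are at stake. The serum results, which with body composition carry the primary aims, may be reported as all-randomised when they are not. And matching ITT and PP results could be read as mutual support when they come from the same data.

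**Working it through.** **Inputs.** 25 women per group and 20% attrition (Sample size); blood at baseline and end only (Measurements); population definitions, change formula and tests (Statistical analysis).

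**Step 1: the plan's own figure.** With the stated hs-CRP means and SDs, the difference is 14.30 − 10.50 = 3.80 and the mean variance is (2.90² + 2.40²)/2 = 7.085, so the SD is 2.66. For two-sided α = 0.05 (sidedness is not stated) and 80% power, n = 2 × (1.960 + 0.842)² × 7.085 / 3.80² = 7.7, hence 8 per arm, and 8/0.8 = 10 after attrition. The t-based version gives 9, then 12. The stated 25 is not reproduced. That is a separate matter and does not bear on this point, which uses only the 25 and the 20%.

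**Step 2: women expected without an end value.** Assume that attrition means no end sample, which the text does not spell out. Then 50 × 0.20 = 10 women are missing and 25 × 0.80 = 20 per arm remain, 40 in all.

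**Step 3: what each listed method needs.**

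| Method | Needs an end value? |
|---|---|
| Percentage change (E − B)/B × 100 | Yes, undefined without E |
| Independent t test or Mann-Whitney on end values or changes | Yes |
| Paired t test or Wilcoxon within group | Yes |
| ANCOVA on end value or change | Yes |
| Regression of changes on one another | Yes |

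Serum has no intermediate value that could stand in.

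**Step 4: overlap of the two sets.** Suppose all 40 completers are sampled and m of the 10 non-completers are also sampled at week 8. ITT then uses 40 + m women and PP uses 40, so the PP women make up 40/(40 + m) of the ITT set.

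| m | Women in ITT serum analysis | Women in PP | Shared |
|---|---|---|---|
| 0 | 40 | 40 | 100% |
| 5 | 45 | 40 | 89% |
| 10 | 50 | 40 | 80% |

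Only the last row is the all-randomised analysis that is defined. Without imputation it requires that women who stop are still measured.

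**Step 5: is power the problem?** On the planning inputs, no. By the normal approximation, 20 per arm gives 3.80/(2.66 × √(2/20)) = 4.51 standard errors and power 99.5%; 25 per arm gives 99.9%.

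**Step 6: possible bias, on assumptions only.** Take a true difference of zero, 20% dropout in each arm, dropout random in one arm and, in the other, tied to the outcome through a latent variable with correlation r. The completer difference is then about r × φ(0.842)/0.8 = 0.35r in SD units: 0.10 for r = 0.3, 0.18 for r = 0.5 and 0.35 in the extreme case where the worst 20% all leave. Nothing in the documents says which r applies.

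**The case against.** The strongest reply is that this is a condensed article. How missing values are handled, and any numerical adherence cut-off, are commonly left to a full protocol or analysis plan that is not shown. That stands: the lack of a named imputation method is not in itself an error here.

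Some stronger readings are tempting, and the text does not support them.

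- A reader might infer that the ITT result cannot be produced at all. It can: the same tests run on all randomised women if end values are collected or imputed, and nothing in the article prescribes a complete-case analysis.
- A reader might infer that a completer analysis is being labelled ITT. The article defines ITT correctly and contrasts it with completers.
- A reader might infer that the two analyses necessarily become one. A woman who stops the capsules but gives an end sample is in ITT and not in PP, and no section says such women go unsampled. The 20% is a planning allowance, not a statement that 10 women will be absent.
- A reader might put the bias at 25%, by supposing that dropouts on taurine gain nothing, so that 3.80 among completers becomes 3.80 × 0.8 = 3.04 among all randomised. That supposition, and the use of a planning difference as a completer effect, are not in the documents.

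It can also be argued that completing the intervention implies taking the capsules and keeping to the diet, since that is what the intervention consists of. This has some force: the text does not say that any woman who reaches week 8 qualifies whatever she took. But it gives no criterion by which a partly adherent woman would be left out.

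Two parts of the concern survive. The PP definition is stated, not left open, and it rests on completion although compliance information is being gathered. And whether women who stop are still measured is a matter of trial conduct: a later analysis plan cannot recover a sample that was never drawn.

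**Conclusion.** The point holds in a conditional form. PP is fixed by completion of 8 weeks with no explicit adherence criterion. Given baseline-and-end serum sampling, tests that all need an end value, and an allowance of about 10 of 50 women lost, the ITT and PP serum analyses will share 80% to 100% of their women. They are identical if non-completers are neither measured nor imputed. In that case, agreement between them would not show robustness.

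This assumes that attrition means a missing end sample and that completers are sampled. It is confined to the serum outcomes, because the article's text does not tie the body-composition measurements to time points in the same way. The issue is possible bias and interpretation, not power. The size of any bias depends on who drops out and why, and the documents do not give it.

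**What to change.** 1. State that every randomised woman is invited to the week-8 measurements and blood draw, whether or not she stopped the capsules or the diet. This must be settled before follow-up begins.
2. Name the all-randomised analysis as primary, using ANCOVA of the end value adjusted for its baseline. Add a sensitivity analysis for women who still lack an end value, for example delta-adjusted imputation. Imputing from baseline alone would add little to an ANCOVA that already adjusts for baseline, so the useful part is varying the assumption about those who are missing.
3. Either add a prespecified adherence criterion to PP, or keep the present set and call it completers. The criterion could use the compliance information already collected, or a capsule count when capsules are dispensed every 15 days. The article mentions no capsule returns, so a count would be a new procedure. The cut-off is the sponsor's choice.

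The cost is slightly more follow-up effort, simple adherence recording and a little more analysis. No change in sample size follows from this point.

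### A Kolmogorov-Smirnov pre-test chooses the test for each outcome and all data are summarised as mean ± SD; the inferential cost is small, but a prespecified baseline-adjusted analysis is clearly better

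*Protocol article*

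**What the plan says.** All of the relevant analysis text is in the Statistical analysis section of the protocol article.

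- Gatekeeper: "The data normality will be analyzed using the Kolmogorov-Smirnov test".
- If normality is accepted: "To compare parametric continuous data between and within the groups, the independent sample" *t* test and the paired *t* test are used.
- If it is not: "to compare the differences in asymmetric variables between and within the groups, the Mann-Whitney test and Wilcoxon test will be applied, respectively".
- Summary statistic, with no exception: "All data will be reported as mean ± SD".
- Adjustment: "The analysis of covariance (ANCOVA) test will be used to control confounding variables". No covariate is named and no transformation is mentioned.

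The group size comes from the Sample size section: "Finally, 25 subjects are considered for each group" and "We considered a 20% attrition rate".

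**The concern.** The rule looks at the outcome data and then decides whether means or ranks are compared. A normality test has little power in a small trial, so a clearly skewed marker can be sent down the t-test route by chance, and a similar marker down the rank route. The two routes do not estimate the same thing, so the treatment effect reported for an outcome depends on the sample drawn.

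The summary rule adds a mismatch that needs no calculation. The section expects some variables to be asymmetric and gives them rank tests, yet describes them by a mean and SD, which those tests do not address.

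At stake are the clarity of what is estimated for each serum marker and some power on markers that turn out to be skewed.

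**Working it through.** **Group size.** 25 per arm less 20% attrition is 25 × 0.8 = 20, so the range is 20 to 25 per arm. The stated inputs do not reproduce the 25. Pooled variance is (2.90² + 2.40²)/2 = 7.085, SD 2.66, difference 14.30 − 10.50 = 3.80. This gives n = 2 × (1.96 + 0.84)² × 7.085/3.80² ≈ 7.7, so 8 per arm, and 8/0.8 = 10 after attrition. That is a separate matter. Only the planned group size is used below.

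**How often skewed data pass.** The statistic is D = max |Fₙ(x) − Φ((x − mean)/SD)|, with mean and SD estimated from the sample. It was judged at 5% in two ways: with the plain asymptotic p value, and with a Lilliefors-type critical value simulated under normality. The article does not say which applies. Samples were lognormal, 20,000 per setting, tested in a single arm. The log-SD is an assumption throughout.

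| log-SD | Lilliefors, n = 20 / 25: pass | Uncorrected, n = 20 / 25: pass |
|---|---|---|
| 0.5 | 66% / 58% | 99% / 98% |
| 0.75 | 40% / 29% | 95% / 90% |
| 1.0 | 21% / 12% | 84% / 73% |

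If both arms must pass before the t test is used, the Lilliefors figures fall to 44% / 35%, 16% / 8% and 5% / 2%. With both arms pooled (n = 40 / 50) and Lilliefors, 39% / 29% pass at log-SD 0.5 and 2% / 0.5% at 1.0.

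**What the two-stage rule costs.** The rule was simulated as t test if both arms pass and Mann-Whitney otherwise, with a true shift of 0.8 log-SD and no baseline covariate.

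| n per arm, log-SD | Log-scale t | Two-stage, uncorrected | Two-stage, Lilliefors |
|---|---|---|---|
| 20, 0.5 | 69.6% | 64.9% | 68.2% |
| 20, 0.75 | 69.2% | 61.8% | 67.3% |
| 20, 1.0 | 69.6% | 61.9% | 67.5% |
| 25, 0.5 | 79.0% | 74.7% | 77.1% |
| 25, 0.75 | 78.6% | 73.0% | 76.1% |
| 25, 1.0 | 79.4% | 74.5% | 76.8% |

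The loss against the log-scale t test runs from 69.6 − 68.2 = 1.4 points to 69.6 − 61.9 = 7.7 points. Under the null, the two-stage rule rejects in 4.7% to 5.6% of trials.

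**The sizing outcome.** The hs-CRP figures give CVs of 2.90/14.30 = 0.20 and 2.40/10.50 = 0.23. If lognormal, log-SD = √ln(1 + CV²), which is 0.20 and 0.23. At log-SD 0.22, with 20 per arm and a 0.9 log-SD effect, power is 78% for the raw t test, 78-79% for the two-stage rule and 79% for the log-scale t test. Nothing material is lost.

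**Where the larger gain comes from.** The scenario has 20 per arm, a 0.9 log-SD effect, baseline correlation 0.5 and log-SD 0.8, all assumed.

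- Planned two-stage rule on end values: 73% (uncorrected) to 77% (Lilliefors).
- Log-scale t test without a pre-test: 79%.
- Log-scale ANCOVA with baseline as covariate: 89%.

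Dropping the pre-test accounts for 79 − 77 = 2 to 79 − 73 = 6 points, and baseline adjustment for 89 − 79 = 10.

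A closed form agrees. Without baseline, 0.9 × √(20/2) = 2.85, and Φ(2.85 − 2.02) ≈ 0.80. With baseline, the residual variance falls by the factor 1 − 0.5² = 0.75, so (0.9/√0.75) × √10 = 3.29, and Φ(3.29 − 2.03) ≈ 0.90.

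Over log-SD 0.5 to 0.8 the two-stage rule gives about 73-79%, against about 89% for log-scale ANCOVA.

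**The case against.** The strongest reply is that the rule does little harm. Where skew is mild enough to be missed, the t test loses little. Where it is strong, a Lilliefors-corrected test usually finds it, and Mann-Whitney is then nearly as powerful as a log-scale test. Type I error is controlled. This stands, and it limits the point to analysis quality.

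The reply also notes that no skewness is given for any marker, so how often skew is missed depends on an assumed shape. It depends too on the version of the test and on whether arms are pooled. That also stands.

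A third reply is that the plan already has ANCOVA, not restricted to normal variables, and that an article may leave its covariates to a fuller document. The missing covariate list is therefore not held against the plan. But ANCOVA is presented as confounder control alongside the pre-tested comparisons, and without a transformation it does not recover the gain under marked skew. Baseline-adjusted ANCOVA on the raw scale reached about 74% at log-SD 0.8, against 89% on the log scale.

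Two stronger readings are tempting. A reader might set a raw end-value t test (about 64-69% in the log-SD 0.8 scenario) against log-scale ANCOVA (89%) and blame the pre-test for 20 points or more. The plan does not use the raw t test regardless, because variables failing the pre-test go to Mann-Whitney, and most of the remaining gap is baseline adjustment. A reader might also infer lost power on hs-CRP, the outcome used for sizing. The article's own figures, with CVs of 0.20-0.23, do not show that.

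**Conclusion.** The point holds as a moderate weakness that should be corrected. It does not threaten the validity of the trial. Two parts rest on the text alone: the test for each outcome is chosen by a pre-test on the same data, and variables treated as asymmetric are still summarised as mean ± SD.

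The size rests on assumptions. For lognormal data with log-SD 0.5, about 58-66% of single-arm samples pass with Lilliefors and 98-99% without. The resulting cost is about 0-8 power points against a prespecified log-scale test, with type I error near 5%. The rise to about 89% power further assumes a 0.9 log-SD effect and a baseline correlation of 0.5, and comes mainly from the covariate. A claim that skewed markers will often be mishandled whatever their shape would go beyond the article. Strong skew (log-SD 1.0) passes in only 12-21% of single-arm Lilliefors tests.

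**What to change.** Replace the pre-test rule with a fixed analysis for each outcome.

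- Drop the Kolmogorov-Smirnov test as a selector.
- Name in advance the markers expected to be right-skewed, for example hs-CRP, TG, insulin, HOMA-IR, FGF21 and the liver enzymes. The article does not establish their skewness, so the team should settle the list from assay experience before unblinding.
- Analyse these on the log scale by ANCOVA with the log baseline value as covariate. Report geometric means and the between-group ratio with 95% CI.
- Analyse the other outcomes by untransformed baseline-adjusted ANCOVA.
- Check residuals, and keep a rank-based comparison as a sensitivity analysis.
- Limit mean ± SD to outcomes analysed on their original scale.

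This changes statistical wording only, with no extra participants, visits or samples. The small downside is that results for the skewed markers are expressed as ratios.

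### The stated between-arm tests are unadjusted and their scale is not fixed; a baseline-adjusted ANCOVA named as the deciding analysis would be more precise at no cost

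*Protocol article*

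**What the plan says.** All the relevant analysis text is in the Statistical analysis section of the protocol article.

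- For normally distributed data, the between-arm test is a two-sample t test without covariates: "To compare parametric continuous data between and within the groups, the independent sample" t test is paired there with a within-group paired t test.
- For skewed data: "to compare the differences in asymmetric variables between and within the groups, the Mann-Whitney test and Wilcoxon test will be applied, respectively".
- The choice between the two is made on the trial data: "The data normality will be analyzed using the Kolmogorov-Smirnov test".
- A further scale is derived: "The percentage changes for each variable will be computed by the following formula", namely end minus baseline, divided by baseline, times 100.
- ANCOVA appears in one sentence: "The analysis of covariance (ANCOVA) test will be used to control confounding variables". The variables are not listed.
- A threshold of p < 0.05 applies throughout, and no analysis is named as the deciding one.

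Two other sections matter. Under Measurements, blood is drawn after an "overnight fast at the baseline and end of the study", so each blood outcome has its own baseline. Under Randomization and blinding, participants are "stratified based on age (within 10-year intervals) randomly into two groups", but age is not named in the analysis.

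**The concern.** In a randomised trial, any confounding at baseline is a matter of chance. The main reason to use ANCOVA is to remove outcome variation that the baseline value predicts, which also corrects for chance baseline imbalance. The article instead makes tests without covariates the between-arm comparison and keeps ANCOVA for unnamed confounders.

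Two things are at stake. The first is precision, in a trial that expects about 20 completers per arm. The second is that several p values for the same outcome can stand side by side (end value, change, possibly percentage change, and ANCOVA) with no rule for which one counts.

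**Working it through.** **Inputs from the article (Sample size).** 25 women per arm and 20% attrition, so 25 × 0.8 = 20 completers per arm; α = 0.05 (taken as two-sided) and 80% power; hs-CRP means 14.30 and 10.50, SDs 2.90 and 2.40.

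**Assumptions.** The article gives no baseline-to-end correlation r, so r = 0.3 to 0.8 is shown. It gives no effect size for outcomes other than hs-CRP, so 0.6 SD is used for illustration. Equal SD at baseline and end is assumed.

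**The article's own figure.** The hs-CRP difference is 3.80 and the pooled SD is √((2.90² + 2.40²)/2) = 2.66, a standardised difference of 1.43. The normal formula gives 8 per arm (9 by noncentral t), or 10 to 12 after attrition. The stated 25 is not reproduced; it exceeds what its inputs require. That is a separate matter. What counts here is that, at 20 per arm, an unadjusted t test already has about 99% power for that difference.

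**Residual variance of each analysis**, in units of the outcome variance:

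- End value: 1
- Change: 2(1 − r)
- ANCOVA on baseline: 1 − r²
- ANCOVA relative to change: (1 − r²)/(2(1 − r)) = (1 + r)/2

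Power is for 20 per arm and a 0.6 SD effect (normal approximation).

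| r | ANCOVA vs end value | ANCOVA vs change | Power: end value | Power: change | Power: ANCOVA |
|---|---|---|---|---|---|
| 0.3 | 0.91 | 0.65 | 47.5% | 36.1% | 51.2% |
| 0.5 | 0.75 | 0.75 | 47.5% | 47.5% | 59.1% |
| 0.7 | 0.51 | 0.85 | 47.5% | 68.8% | 75.7% |
| 0.8 | 0.36 | 0.90 | 47.5% | 85.1% | 88.5% |

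ANCOVA is ahead of both unadjusted tests in every row. The two unadjusted tests change places at r = 0.5, so without knowing r nobody can say which of them is the better choice. Against the better of the two, 20 women per arm analysed by ANCOVA are worth 20/0.91 = 22.0 at r = 0.3, 20/0.75 = 26.7 at r = 0.5, 20/0.85 = 23.5 at r = 0.7 and 20/0.90 = 22.2 at r = 0.8. Against the worse, they are worth 20/0.65 = 30.8 at r = 0.3 and 20/0.36 = 55.6 at r = 0.8.

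**Simulation check, normal data** (2,500 runs, slope estimated, 0.6 SD). Power for end value / change / ANCOVA was 45 / 34 / 48% at r = 0.3, 48 / 46 / 58% at r = 0.5 and 45 / 65 / 72% at r = 0.7. The ordering is the same and the levels are slightly lower.

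**Simulation check, skewed data** (log-normal, log-SD 0.8, r = 0.5, 0.6 SD decrease on the log scale). Power was 37% for the t test on percentage change, 44% for Mann-Whitney on percentage change, 45% for Mann-Whitney on end value and 57% for log-scale ANCOVA.

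**Type I error.** With no true effect, each test alone rejected in about 5% of runs (4.6 to 6.1%). The chance that at least one of end-value t, change t, percentage-change t and ANCOVA reached p < 0.05 was 9.5%, 11.5% and 9.9% for normal data at r = 0.3, 0.5 and 0.7, and 11.9% for log-normal data at r = 0.5. That is about 10 to 12% for one outcome.

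**The case against.** Unadjusted t and Mann-Whitney tests are valid under randomisation, so nothing in the section is a false statement. That stands: this is a point about a better method and a fixed choice, not about validity. The unnamed confounders might include the baseline value, and a covariate list may sit in a full protocol or SAP that is not shown. That is also fair, and the absence of a list is not the complaint. The article does state unadjusted tests as the comparison and gives ANCOVA a different purpose; an added list would not by itself make the adjusted result the deciding one.

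The size of the gain is open to challenge too. It depends on an r that the article does not give, and for the hs-CRP difference that sized the trial there is almost nothing to gain. Both limits are accepted. FGF19, FGF21 and β-klotho, however, have no stated effect assumption, so the 99% power does not carry over to them.

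A reader might infer more than the text supports:

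- *That the arms will be tested on percentage change.* The article says only that these changes are computed, and they may be descriptive.
- *That percentage change is generally inefficient.* It is not. In a log-normal simulation with log-SD 0.5, r = 0.7 and an effect of 0.9 SD, it matched raw-scale ANCOVA at about 94% power.
- *That the baselines are thrown away.* A change score uses the baseline, though less efficiently than ANCOVA; only an end-value test ignores it.
- *That the sponsor plans to adjust for on-study diet, activity or weight.* The wording does not exclude this, but nothing proposes it, and diet and activity are also measured at baseline.

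**Conclusion.** The point holds as one of efficiency and pre-specification. The stated between-arm comparison takes no covariates, its scale is not fixed, and ANCOVA is assigned to confounding without the outcome's baseline being named, although that baseline is collected. The variance ratio in favour of ANCOVA is 0.91, 0.75, 0.51 and 0.36 against end value, and 0.65, 0.75, 0.85 and 0.90 against change, at r = 0.3, 0.5, 0.7 and 0.8. These ratios rest on equal SDs and an assumed r. The gain is minor at the low end of r against end value, at the high end against change, and for the hs-CRP design difference.

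The 10 to 12% error rate describes an analyst who takes the best of several scales after seeing the data. The article does not say that this will happen, and each analysis alone keeps about 5%. The change should be made, because it improves precision across the whole range of r and closes the choice of scale.

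**What to change.** In the Statistical analysis section, name one deciding between-arm analysis per outcome: an ANCOVA of the 8-week value (log scale for skewed markers) on arm, with that outcome's baseline value and the age stratum as covariates. State that only covariates measured before randomisation may enter. Report the adjusted difference with a 95% confidence interval. Keep the unadjusted t and Mann-Whitney tests as supportive, and show percentage change as a descriptive column without a p value.

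The cost is wording only: the planned data and software already support this analysis. The baseline covariate uses one degree of freedom, and the age strata a few more.
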